## Abstract

Supplemental Digital Content is available in the text

## Introduction

1

The safety and efficacy of antiplatelet therapy in secondary prevention of wide-ranging cardiovascular risk (coronary artery disease, stroke-related outcomes, and peripheral vascular disease) have been well established from some systematic studies and meta-analysis^[1,2,3,4,5,6,7,8,9]^ This has resulted in their incorporation into most national and international treatment guidelines.^[10,11,12]^ Recently, concerns have been raised regarding the potential of attenuation of aspirin pharmacokinetic (PK) effects following administration in an EC formulation.^[13,14,15,16,17,18]^ The recurrence of stroke and ischemic heart disease (IHD)-related outcomes have been a subject of concern over the past few years. Anti-platelet therapy resistance has been a particular subject of such concern.^[19,20,21]^ Aspirin resistance whilst secondary to several factors appears in recent reports to be influenced by amongst others its enteric coating. Various systematic and mechanistic studies have explored the effect of enteric coating on aspirin effectiveness.^[13,14,16,17,18]^ Whilst the outcomes of these reports have not been uniform or unanimous, it raises considerable concern regarding the propensity of enteric coating to significantly attenuates its level and reduce its effectiveness in primary and secondary prevention. In a seminal mechanistic report, showed significantly low TXB2 level (a surrogate marker of aspirin response) in obese type 2 DM patients on EC Aspirin compared to their sex and age-matched cohorts on plain aspirin.^[16]^

Despite the evident limitation of this report (been a proof of concept study with a mechanistic design), uncertainty remains regarding the impact of this on long-term hard cardiovascular outcomes. In this study, we aim to firstly validate this reported association in a population of stroke patients, and in subsequent prospective studies ascertain the effect of enteric coating of aspirin on hard clinical endpoints such as the major adverse cardiovascular events (MACE).

## Methods/design

2

### Study design and settings

2.1

This is an open-label, two-arms, parallel, non-randomized (consecutive patients’ randomization) proof of concept, phase 4 pharmacokinetic/ pharmacodynamic study. We will recruit eligible patients from the stroke unit of designated recruitment centers (Hamad General Hospital). Patients who satisfy pre-specified inclusion criteria will be invited to participate in the study. Patients who agreed to take part will be screened, counseled, and enrolled in the study. They will be required to sign a consent form before allocation. This study was approved by the local MRC and The Institutional Review Board (IRB) (Hamad Medical Corporation, **MRC number: 01–18–156**) and registered in clinicaltrials.gov (NCT04330872) (Fig. 1).

**Figure 1 F1:**
[figure not shown]
Flow chart depicting the study procedures.

### Setting and participants

2.2

Patients (male and female) (N = 42) with newly diagnosed ischemic stroke who are just to start aspirin therapy, and who attend stroke units of designated recruitment centers (Hamad General Hospital). We will enroll participants meeting the following inclusion criteria:

#### Inclusion criteria

2.2.1

1.Newly diagnosed ischemic stroke who are just about to start Aspirin.2.No prior history of cardiovascular morbidity (including IHD, chronic kidney disease, peripheral vascular disease)3.18 to 75 years.

#### Exclusion criteria

2.2.2

1.Concomitant antiplatelet therapy (irrespective of the duration of the treatment).2.Patients on any prostaglandins-related medications (non-steroidal anti-inflammatory drugs, misoprostol, and other ant secretory drugs among others).3.Any salicylate-containing supplements.4.Patients on the NG tube will be excluded from the study.

### Randomization, allocation concealment, and blinding

2.3

Consecutive patients meeting the eligibility criteria will be explained about the study procedures by one of the trial investigators following that that patient will be consented by designated study investigators (Supplementary materials 1. Consent form). If the patient consents to participate in our trial, then he/she will be allocated to either plain or EC aspirin arms following their admission order. Outcome assessors and data analysts are blinded to patient allocation.

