### Interventions

2.4

Once allocated to one of the two study arms, the study participants will be administered the study medication as either enteric-coated or plain Aspirin on day 1. Patients assigned will be prescribed plain loading dose (Dispersible 300 mg stat followed by Aspirin 75 mg tablets, Actavis UK Ltd) or EC Aspirin loading dose (300 mg stat followed by100 mg, Bayer, Germany) for 3 days (study duration). Irrespective of the design of the study, all patients enrolled in the study will receive other standards of care management according to HMC ischemic stroke guidelines. Patients will be required to give blood samples (10 mL) for estimation of the TXB2 level at baseline and on day 3, which marks the end of the study. Blood samples will be taken as part of the patient's routine investigation/care by the phlebotomist. Study samples will be taken by a designated study investigator as per standard protocols consistent with HMC guidelines. Study samples will be kept in labeled with anonymous patient-specific identifiers and kept in study refrigerators until completely used. Patients will be kept on other treatments constituting the usual standards of care management for established ischemic stroke, and this will be maintained throughout the study. We anticipate that it would take about one month to complete patient recruitment. Following the end of the study, laboratory analysis of biological samples will be carried out within 3 weeks with subsequent data evaluation and analysis.

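### Section 2.3 promises randomization and concealment, but its only rule is admission order, which is neither random nor concealed, so the arm can be foreseen at consent

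*Protocol article*

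**What the plan says.** All references are to the protocol article.

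- **Design label (section 2.1).** The study is described as "open-label, two-arms, parallel, non-randomized (consecutive patients’ randomization) proof of concept, phase 4 pharmacokinetic/ pharmacodynamic study". One phrase both denies and claims randomization.
- **Allocation rule (section 2.3).** The heading names randomization, allocation concealment and blinding. The text gives one rule: on consenting, the patient "he/she will be allocated to either plain or EC aspirin arms following their admission order". It mentions no random sequence, list holder or concealment step.
- **Who recruits (section 2.3).** Consecutive eligible patients "will be explained about the study procedures by one of the trial investigators following that that patient will be consented by designated study investigators".
- **Order of steps (section 2.1).** "They will be required to sign a consent form before allocation".
- **Blinding (sections 2.3 and 2.4).** "Outcome assessors and data analysts are blinded to patient allocation". The supporting measure given is that samples are "labeled with anonymous patient-specific identifiers".

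**The concern.** An article may leave the details of sequence generation to a fuller protocol. Here, however, the mechanism is stated, and what is stated is the problem. Admission order exists before anyone approaches the patient. Taking consent before allocation therefore conceals nothing if the arm follows from that order. Treatment is open, so staff also see earlier assignments.

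Two things are at stake. The first is selection: someone who foresees the arm can, knowingly or not, read a borderline eligibility criterion more or less strictly, or present the study more or less persuasively. The exclusion for prostaglandin-related drugs (section 2.2.2) is open-ended, so it leaves some room for judgement. The second is how the result will be read. Section 2.8.2 plans an intention-to-treat primary analysis, and the Discussion says that a TXB2 difference would invite trials on hard clinical outcomes. A causal comparison between arms is intended, and the words randomization and concealment give it a strength that the rule does not supply.

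**Working it through.** **1. Comparison of the stated steps**

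| Step | What the article says | Consequence |
|---|---|---|
| Sequence | Admission order | No random element |
| Concealment | In the heading only | The order is visible before consent |
| Consent | Taken by trial investigators, before allocation | The person seeking consent can foresee the arm |
| Treatment | Open-label | Past assignments are visible |

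The article does not say who judges eligibility. I assume that it is trial or unit staff who know the rule.

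**2. What admission order could mean.** The article does not specify the scheme. Two simple readings cannot both apply:

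- *Strict alternation:* every assignment after the first is known, which is 42 − 1 = 41 of 42.
- *First 21, then next 21:* arm is confounded with calendar time and with sample storage time. Section 2.4 expects about one month of recruitment, with laboratory analysis within 3 weeks of the study's end. If recruitment is even, the arms' mean enrolment dates differ by about half a month (¾ − ¼).

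The arm is foreseeable under either reading, but the two figures belong to different schemes.

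**3. Weight of one patient.** With 21 per arm (section 2.8.1), one patient is 1/21 = 4.8 percentage points of an arm's non-responder rate, and two are 2/21 = 9.5 points. The second figure is a ceiling: it needs both patients to be non-responders in place of responders.

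**4. Yardstick from the plan's sample size.** The 21 per arm cannot be reproduced uniquely, because the article gives no standard deviation (SD). Solving backwards for 80% power and two-sided alpha 0.05, with the normal approximation:

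d = (1.960 + 0.842) × √(2/21) = 0.865 SD

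The t-test version gives 0.886. The allocation point does not depend on this figure. It serves only as a scale for step 5.

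**5. Illustration of possible bias (assumed inputs).** Suppose that there is no true effect, that the sequence is fully foreseen, and that the prognosis of enrolled patients shifts by +η SD in one arm and −η SD in the other. The bias is 2η, and the two-sample t statistic (40 df) has noncentrality 2η/√(2/21) = 2η/0.3086.

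| η (assumed) | Bias (SD) | Noncentrality | Type I error (nominal 0.05) |
|---|---|---|---|
| 0.1 | 0.2 | 0.65 | 0.10 |
| 0.2 | 0.4 | 1.30 | 0.24 |
| 0.3 | 0.6 | 1.94 | 0.48 |
| 0.5 | 1.0 | 3.24 | 0.89 |

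Simulation (6,000 trials each) gave 0.235 and 0.481 at η = 0.2 and 0.3. With a concealed random sequence, where the recruiter's guess is a coin flip, it gave 0.055 and 0.054. At η = 0.2 the bias is 0.4/0.865 = 46% of the difference that the trial is sized to detect. The model uses a continuous outcome, not the binary primary outcome. No value of η can be taken from the article.

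**The case against.** The defence has real force on several points.

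- **The design is disclosed.** Section 2.1 calls the study non-randomized and proof of concept. That stands, but the same phrase and the heading of section 2.3 say the opposite.
- **Patients are approached consecutively.** A reader might infer that investigators can choose whom to approach and when. The text does not support that: eligible patients are taken consecutively, and delaying an approach would not obviously change an arm tied to admission order. What remains is eligibility judgement and consent, a narrower route that is still open.
- **Admission order might only set the place on a random list.** This is the kindest reading of the bracket in section 2.1. No list is mentioned, and it does not fit the word non-randomized. If it is what was meant, the text still has to say so.
- **Assessors are blinded and the primary outcome is a laboratory value.** A reader might infer that the rule defeats this blinding. The article does not show that. Samples carry anonymous codes, and nothing says that the codes follow enrolment order. The blinding is easier to break only if sample codes or analysis data reveal that order. Equally, a blinded assay cannot prevent selection at enrolment.
- **Baseline data help.** Baseline TXB2 is measured, the non-responder definition includes percent inhibition, regression is planned, and patients with nasogastric tubes are excluded. These measures reduce measured imbalance. They cannot be relied on to remove unmeasured selection in 42 patients.
- **The error rates above are assumed.** This is correct. They show sensitivity to selection and do not estimate what would happen.

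**Conclusion.** The point holds in this form. The stated rule is neither random nor concealed, it contradicts the heading of section 2.3, and section 2.1 contradicts itself. The arm is foreseeable to those taking consent, so selection bias can enter through eligibility judgement and consent despite the consecutive approach. This assumes that staff know the rule and that no undisclosed random list lies behind it.

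The size of the bias cannot be derived from the article. The weight per patient (4.8 points) follows from 21 per arm. The 41-of-42 figure requires alternation, and the confounding with calendar time requires 21-then-21. A reader might take the two figures together, or take the illustrative error rates as a forecast. The article supports neither.

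**What to change.** **If enrolment has not begun,** replace the admission-order rule in section 2.3 with text to this effect:

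> Patients are randomised 1:1 from a computer-generated list in permuted blocks of varying size. The list is held by pharmacy, or the assignments are kept in sequentially numbered opaque sealed envelopes. Each assignment is released only after consent and the baseline sample.

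Correct section 2.1 to call the design randomised. State that sample codes are unrelated to enrolment order, and that the data given to blinded analysts do not reveal it.

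**If patients have already been enrolled by admission order,** delete randomization from section 2.1, and randomization and allocation concealment from section 2.3. State the exact scheme used, describe the study as a non-randomised (quasi-experimental) comparison, and limit the causal conclusion in the Discussion accordingly. Past-tense wording in sections 2.5 and 2.9 suggests, without proving, that the study had started.

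**Cost.** Before enrolment, this needs one amendment, a list, and envelopes or pharmacy release, with a possible imbalance of a few patients from variable blocks. N stays at 42. During enrolment, a switch would mix two allocation methods, so relabelling may be the only workable course. It costs only wording, but it leaves the selection risk in place.

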### Interventions

2.4

Once allocated to one of the two study arms, the study participants will be administered the study medication as either enteric-coated or plain Aspirin on day 1. Patients assigned will be prescribed plain loading dose (Dispersible 300 mg stat followed by Aspirin 75 mg tablets, Actavis UK Ltd) or EC Aspirin loading dose (300 mg stat followed by100 mg, Bayer, Germany) for 3 days (study duration). Irrespective of the design of the study, all patients enrolled in the study will receive other standards of care management according to HMC ischemic stroke guidelines. Patients will be required to give blood samples (10 mL) for estimation of the TXB2 level at baseline and on day 3, which marks the end of the study. Blood samples will be taken as part of the patient's routine investigation/care by the phlebotomist. Study samples will be taken by a designated study investigator as per standard protocols consistent with HMC guidelines. Study samples will be kept in labeled with anonymous patient-specific identifiers and kept in study refrigerators until completely used. Patients will be kept on other treatments constituting the usual standards of care management for established ischemic stroke, and this will be maintained throughout the study. We anticipate that it would take about one month to complete patient recruitment. Following the end of the study, laboratory analysis of biological samples will be carried out within 3 weeks with subsequent data evaluation and analysis.

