### Primary outcomes

2.6

Incidence of Aspirin non-responders at day 3 (level of residual serum TXB2 associated with elevated thrombotic risk (<99.0% inhibition or TXB2 >3.1 ng/mL).

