#### Sample size

2.8.1

There are no previous studies to allow for a robust estimation of the study sample size. However, given that this is proof of concept study, we estimated that a sample size of 21 patients in each arm of the study would yield an approximate 80% power to detect 50% difference in population mean, for two-sided significance and an alpha level of 0.05.

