## Discussion

3

Our study is the third study assessing the possible effect of enteric-coated aspirin formulation on TXB2 inhibition. The first study was in 2006 by Cox et al. In their study of seventy-one healthy volunteers taking both Plain and EC aspirin in a randomized crossover design, they concluded that EC aspirin was not as effective as plain Aspirin in terms of TXB2 inhibition. The second study was in 2017 by Bhatt et al. It examined 40 diabetic patients in a randomized crossover design. Again, it concluded the inferiority of EC aspirin formulations compared to plain Aspirin (High proportion of incomplete TXB2 inhibition).

The findings from the previously mentioned trials prompted us to perform the first trial (up to the best of our knowledge), examining the level of TXB2 inhibition in stroke patients taking various formulations of Aspirin (plain vs EC aspirin). If a difference is TXB2 is found in our trial, this significant finding will invite additional clinical trials exploring the efficacy of various formulations of Aspirin measured via hard clinical outcomes such as major adverse cardiovascular events (MACE).

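### Maintenance dose differs by arm (75 mg plain, 100 mg enteric-coated), so a null or small TXB2 difference cannot exclude a coating effect

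*Protocol article*

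**What the plan says.** The Introduction is concerned with enteric coating reducing the effect of aspirin, and says of the reported link that "we aim to firstly validate this reported association in a population of stroke patients". The Discussion places the trial among studies "assessing the possible effect of enteric-coated aspirin formulation on TXB2 inhibition". The factor of interest is the coating.

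Interventions (2.4) sets the regimens. The plain arm receives "Dispersible 300 mg stat followed by Aspirin 75 mg tablets, Actavis UK Ltd". The EC arm receives "300 mg stat followed by100 mg, Bayer, Germany". The load is 300 mg in both arms; the maintenance dose is 75 mg in one and 100 mg in the other. The same section provides for "estimation of the TXB2 level at baseline and on day 3, which marks the end of the study". Primary outcomes (2.6) then names "Incidence of Aspirin non-responders at day 3".

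**The concern.** A comparison meant to show what coating does should hold the dose constant. Here every EC patient takes 100 mg and every plain patient 75 mg. The larger dose goes to the arm expected to inhibit TXB2 less, so any benefit from the extra 25 mg would offset part of the disadvantage the trial is looking for.

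At stake is the reading of a null or small difference. It could mean that coating matters little, or that a real coating effect was partly offset by dose. Imprecision shows up in the width of a confidence interval. This bias would not, because it shifts the quantity being estimated.

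**Working it through.** **The plan's own figure.** Sample size (2.8.1) says that "a sample size of 21 patients in each arm of the study would yield an approximate 80% power" for a 50% difference in means, two-sided alpha 0.05. No standard deviation is given, so the figure cannot be reproduced from stated inputs. By the normal approximation, 21 per arm at 80% power implies a standardised difference of (1.960 + 0.842) × √(2/21) = 0.865, that is, a coefficient of variation of 0.5/0.865 = 0.58. The present point does not depend on this figure.

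**Inputs, all from Interventions (2.4).** Load 300 mg in both arms; maintenance 75 mg (plain) and 100 mg (EC); two manufacturers; dispersible load in the plain arm; TXB2 sampled at baseline and day 3.

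**Step 1: what the arm contrast estimates.** Take residual TXB2, or non-response on a suitable scale, with higher values worse. Write β for the effect of coating, δ for the effect of 100 mg instead of 75 mg maintenance, μ for manufacturer and λ for the non-dispersible load. All four factors change together between the arms, so

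EC minus plain = β + δ + μ + λ.

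Only this sum can be estimated. In the regression described under Statistical analysis (2.8.3), a dose term would equal 75 + 25 × (EC indicator). It is an exact linear function of arm, so dose and arm cannot both be fitted.

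**Step 2: direction.** Assume that more aspirin gives at least as much suppression, so δ ≤ 0. Then β + δ ≤ β, and the dose gap can only shrink an EC disadvantage.
- An observed sum near zero is compatible with β > 0 offset by δ < 0.
- An observed sum above zero cannot be due to δ. It could still come from μ or λ instead of β.

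**Step 3: size of the dose gap.** The maintenance ratio is 100/75 = 1.33. Cumulative dose by the day-3 sample depends on how many maintenance doses come before it:

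| Doses before the sample | Plain (mg) | EC (mg) | EC excess |
|---|---|---|---|
| Load + 1 | 300 + 75 = 375 | 300 + 100 = 400 | 400/375 = 1.067, +6.7% |
| Load + 2 | 300 + 150 = 450 | 300 + 200 = 500 | 500/450 = 1.111, +11.1% |
| Load + 3 | 300 + 225 = 525 | 300 + 300 = 600 | 600/525 = 1.143, +14.3% |

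The first row applies if the load is the day-1 dose and the sample comes before the day-3 dose; the second if the sample follows that dose. The third needs three maintenance doses after the load. The article does not say which applies.

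**Step 4: what cannot be computed.** Turning these excesses into a TXB2 offset needs a dose-response relation for 75 against 100 mg after a 300 mg load. The article gives none, so δ has no numerical estimate here.

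**The case against.** The case for leaving the plan alone has several parts.

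- **The exposure gap is small.** The common 300 mg load dominates three days of dosing, and the 1.33 ratio overstates the contrast over that period. This stands, and it is why no size is claimed for the bias. A small gap in milligrams does not show that its effect on TXB2 is nil.
- **The bias is conservative for the trial's hypothesis.** Under the stated assumption, a finding that EC is worse is not produced by dose. This also stands. The difficulty is confined to a null or small difference.
- **A null would be inconclusive anyway.** With 42 patients allocated by admission order, a coating effect could be missed or confounded even at equal doses. True; the dose gap adds to those limits and does not create them.
- **These are marketed products, openly described, and a reason for the doses may sit in the full protocol.** Both may be so, and nothing here rests on the absence of a rationale. A reason for the doses would not make coating separable from dose.

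A reader might go further and infer that a masked effect would stop the follow-up trials, since the Discussion links them to the condition "If a difference is TXB2 is found in our trial". The text does not support that. It says a difference will invite further trials, not that a null rules them out, and the Introduction announces later prospective studies on clinical endpoints without any condition. Nor can a loss of power be attributed to the dose gap: any such figure would need an assumed offset and would only restate it.

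**Conclusion.** The point holds as a limit on what the trial can conclude about coating. Maintenance dose, manufacturer and the dispersible load are each fully aliased with arm, and no analysis of these two arms can separate them. That follows from the stated regimens and needs no assumption.

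The direction of the dose bias, towards no difference, rests on the assumption that more aspirin suppresses TXB2 at least as much. Its size is unknown and may be small, given an equal load and a cumulative EC excess of about 7% to 11% (14% only with three maintenance doses after the load). A null or small difference therefore cannot exclude a coating effect. On the same assumption, a worse EC result is not explained by dose, but it does not isolate coating. The point is worth correcting because the remedy is specific and, in its wording form, cheap. It is not evidence that the trial will miss an effect.

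**What to change.** **Preferred:** use the same maintenance dose in both arms; which dose is the sponsor's choice. This needs a protocol amendment and a change in study-drug supply, and patients already enrolled would have had the unequal regimen. It removes the dose difference only. Manufacturer and the dispersible load would still differ, so the caution about isolating coating should stay.

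**If supply prevents matching:** in Interventions (2.4), describe the comparison as EC 300/100 mg against plain (dispersible load) 300/75 mg, and word the conclusion in the same terms. Add to the Discussion, for example: *Because the EC maintenance dose is higher, a null or small difference cannot exclude a coating effect. A worse EC result would not be explained by this dose gap, but it would not isolate coating, since manufacturer and the dispersible load also differ by arm.*

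The wording option takes two or three sentences and leaves sample size and analysis unchanged. Its cost is a narrower conclusion, about two regimens instead of coating as such, and the aliasing remains.

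### A refrigerator hold of TXB2 samples, up to about 7 weeks on the more natural reading, exposes the absolute 3.1 ng/mL limb of the primary endpoint to any storage loss

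*Protocol article*

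**What the plan says.** Section 2.4 (Interventions) of the protocol article takes blood for TXB2 "at baseline and on day 3, which marks the end of the study". The samples are "kept in study refrigerators until completely used". No temperature, stability limit or longest permitted storage time is given.

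Two statements in the same section set the waiting time. On recruitment: "We anticipate that it would take about one month to complete patient recruitment". On the assay: "Following the end of the study, laboratory analysis of biological samples will be carried out within 3 weeks".

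Section 2.6 (Primary outcomes) counts a patient as a non-responder at day 3 on "<99.0% inhibition or TXB2 >3.1 ng/mL". A responder must therefore pass both limbs, one relative to baseline and one absolute.

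Section 2.3 (Randomization, allocation concealment, and blinding) says patients are "allocated to either plain or EC aspirin arms following their admission order". It does not say whether the arms alternate or are filled one after the other. It also says: "Outcome assessors and data analysts are blinded to patient allocation".

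**The concern.** TXB2 is the only measurement behind the primary endpoint. The article names a storage method, lets storage time depend on when a patient enrolled, and sets no upper limit on it. If the measured value changes with storage, the two limbs of the endpoint respond differently. The relative limb compares two samples of nearly the same age, so a proportional change almost cancels. The absolute limb compares one stored sample with a fixed number, so nothing cancels.

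With 21 patients per arm, each misclassified patient moves that arm's non-responder rate by 1/21 = 4.8 percentage points. Storage cannot be corrected once the samples have been held, so the method has to be settled before recruitment.

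**Working it through.** The article states no storage duration to reproduce, so the duration is built from its parts.

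**Inputs from the article.** Recruitment about one month, taken as 30 days (section 2.4). Assay up to 3 weeks = 21 days after the end of the study (section 2.4). Samples at baseline and day 3, about 2 days apart (section 2.4). Total N = 42 (section 2.2), 21 per arm (section 2.8.1). Cut-offs 99.0% inhibition and 3.1 ng/mL (section 2.6).

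**Assumptions.** Patients enrol at even spacing. On the first reading there is one common assay date. Any storage change is a proportional loss, of unknown size.

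**1. Storage time, assay after recruitment closes.** Storage = assay date − sample date.
- Assay at once: 0 to 30 days.
- Assay at 3 weeks: 21 to 21 + 30 = 51 days, about 7 weeks.
- Spread between first and last patient: 30 days either way.

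**2. Storage time, assay within 3 weeks of each patient's day 3.** About 21 days at most for the day-3 sample and about 2 days more for baseline. The link with enrolment date disappears.

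**3. Absolute limb.** With fractional loss L, the true value that reads exactly 3.1 ng/mL is 3.1/(1 − L). With the same loss in both samples, measured inhibition equals true inhibition. The patient then passes the relative limb only if the day-3 value is at most 1% of baseline, that is, if baseline is at least 100 times the day-3 value.

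| Assumed loss L | True day-3 value reading 3.1 (ng/mL) | Baseline needed to be reclassified (ng/mL) |
|---|---|---|
| 10% | 3.1/0.9 = 3.44 | 344 |
| 20% | 3.1/0.8 = 3.88 | 388 |
| 30% | 3.1/0.7 = 4.43 | 443 |
| 50% | 3.1/0.5 = 6.20 | 620 |

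True values between 3.1 and the tabulated figure need 100 times their own value, so never less than 3.1/0.01 = 310 ng/mL. Below that baseline the relative limb flags the patient whatever the storage loss.

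**4. Relative limb.** The two samples of one patient differ by about 2 days in age. For assumed drifts of 0.1%, 0.5%, 1% and 2% per day, their ratio moves by exp(2k) − 1 = 0.2%, 1%, 2% and 4%. For scale, a 10% to 50% loss over 51 days is −ln(1 − L)/51 = 0.2% to 1.4% per day.

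**5. Arm difference in mean storage (30 days, 42 patients).** Spacing is 30/41 = 0.73 days.

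| Allocation rule | Difference in mean storage | Correlation of arm with storage | Between-arm shift at 0.1%, 0.5%, 1%, 2% per day |
|---|---|---|---|
| Strict alternation | 0.73 days | 0.04 | 0.07%, 0.4%, 0.7%, 1.5% |
| First 21 in one arm, last 21 in the other | 21 × 0.73 = 15.4 days | 0.87 | 1.5%, 8%, 17%, 36% |

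If recruitment took 20 to 45 days, the differences would be 0.49 to 1.10 days under alternation and 10.2 to 23.0 days with sequential filling.

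**The case against.** **No harm is shown.** Nothing in the article says that TXB2 changes in a refrigerator, so the losses above are assumptions. This stands. It limits the point to an exposure that the plan leaves open, not a demonstrated error.

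**A single batch is not stated.** The article gives a 3-week window, and it also calls each patient's day 3 the end of the study. On that meaning the 7-week figure falls away. This stands as an alternative reading. The assay sentence follows the recruitment sentence, which favours an assay period after recruitment but does not prove it.

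**Storage confounded with arm.** A reader might infer this, because enrolment order governs storage time and admission order governs the arm. The article does not support it as a flat statement: under alternation the arms differ by less than a day. The roughly 15-day difference needs one arm filled first, which the text neither states nor excludes. Blinded assessors do not settle the matter either way, since storage age acts without anyone's judgement.

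**The endpoint is not decided at 3.1 ng/mL alone.** This stands. The inhibition limb still catches patients unless baseline is high, and the article gives no baseline values, so the number at risk is unknown.

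**Laboratory detail belongs in a manual.** This stands for clotting and centrifuging. A reader might infer from their absence that whole blood is stored, but section 2.6 names serum, section 2.4 refers to standard hospital procedures, and an article may leave such steps out. It does not remove the refrigerator hold, which the article does state. If a laboratory manual specifies something else, the two texts must be reconciled.

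**Conclusion.** The point holds in a limited form, as an inexpensive improvement. The article states a refrigerator hold with no time limit for the assay behind the primary endpoint. Whether the longest hold is about 7 weeks or about 3 weeks turns on an ambiguous phrase. Only the absolute limb is materially exposed, only if storage loss occurs, and only in patients whose baseline exceeds 310 ng/mL. Any such loss would mainly add misclassification shared by both arms, in the direction of too few non-responders.

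The documents do not support the stronger conclusions that storage will create a false difference between formulations or that the endpoint is invalid. Those would need stability data, baseline TXB2 values and the allocation rule, and the article gives none of the three. The sizes rest on a 30-day recruitment, even enrolment, a common assay date and an assumed proportional loss.

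**What to change.** - Replace the refrigerator hold with frozen storage of separated serum aliquots until assay, and state the longest permitted storage time.
- Say whether the 3-week assay window runs from each patient's day 3 or from the close of recruitment.
- Assay each patient's baseline and day-3 aliquots in the same run, with both arms in every run.
- Report storage time by arm. Together with a stated admission-order rule, this lets a reader check whether storage was balanced.

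The cost is freezer space and an amendment to the laboratory procedure. No extra patients, blood or visits are needed.
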